### Intervention

As illustrated in Figs. 2 and 3, an 8-week corrective exercises protocol is taken by two intervention groups considering the UCS features such as alignment, muscle activity, and movement pattern simultaneously. The exercise program is performed three days per week to achieve the best results. Each session lasts nearly 50 min, initiating by 5–7 min of warm-ups and finishing by cool-down, respectively [59]. In addition, the exercises are initiated by three repetitions holding for 10 s using the Borg scale [68] and progress to six repetitions, holding for 25 s based on overload principles and individual characteristics [59, 61]. If reporting pain during the exercise performance, the subjects can discontinue and rest until pain relief, while moderating the exercises accordingly. A qualified corrective exercise instructor supervises the exercise programs of both intervention groups. The online-supervised group includes up to four subjects. Each session is remotely performed and supervised three times a week for 8 weeks in their home environment using real-time desktop videoconferencing software (https://meet.jit.si/) via a laptop computer. Accordingly, subjects can have contact and talk with both the instructor and the other subjects [62]. The workplace group performs all sessions in the worksite without daily face-to-face supervision, although supervision is conducted using diary and telephone interviews. Further, each participant in this group is provided with a detailed written exercise and pictorial descriptions to enhance exercise performance. However, the corrective exercise expert is present once a week during the exercise sessions to provide input and evaluate the progress and ensure that all subjects are exercising safely and correctly [49]. It is noteworthy that the corrective exercises protocol is expected to prevent the undesired lack of scapula stabilization on the thorax diminish neck and shoulder pain. Individuals with shoulder pain have excessive upper trapezius activation and decreased and/or delayed activation of the LT, MT, and SA [66]. Thus, exercises specifically targeting the trapezius and SA muscles are commonly incorporated into rehabilitation programs to optimize the scapular position and motion [69]. Recent studies indicated that the specific training of the neck muscles, such as strengthening deep cervical flexor muscles, could reduce neck pain and improve SCM endurance, which is effective in correcting head and shoulder postures [68, 70]. Therefore, these exercises are recommended to improve the function of muscles in the neck, shoulder, and thoracic for several painful conditions due to their reduced or altered activation. At the follow-up, subjects are asked whether they have experienced any injuries or other adverse events during the training sessions.

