## Method

### Study design

A parallel-group randomized control trial with a pretest-posttest design is used for the present study. Additionally, the selected subjects are randomly assigned to three groups including two interventions (i.e., online-supervised exercise and workplace exercise receiving 8 weeks of intervention) and a control group with no intervention performing routine activities. In addition, baseline assessments are organized at the Sports Science and Health Laboratory at Shahid Beheshti University, Tehran, Iran, and are repeated after 8 weeks of intervention. The procedure and flow diagram are shown in Table 1 and Fig. 1, respectively. The procedure is followed according to the SPIRIT^1^ guidelines to ensure the apparent and standardized reporting of the trial.

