### Subjects and eligibility criteria

The corrective exercise specialist (Ph.D.) primarily screens the subjects recruited through invitation letters from private and public organizations in Tehran, Iran, for three main UCS features. Since the presence of scapular dyskinesia may indicate the lack of neuromuscular control, including muscle activation and timing thus, the related tests are performed to evaluate the position and rhythm of the scapula, which plays a significant role in facilitating the upper extremity function among office workers [58–60]. Further, due to any postural alteration influencing the muscle activity, muscle length and muscle strength tests are implemented for UT and pectoral muscles and MT, LT, and deep cervical flexor, respectively [61].

Inclusion criteria for the trial must comply with office workers between 30 and 45 years using a computer or lab-tops most commonly during the working day (about 30 h per week) with at least 5 years of experience [17, 62]. Having alignment alteration includes forward head (≥ 45°), round shoulder (≥ 52°), and round back (≥ 42°) according to previous studies [63, 64]. Marking pain intensity score visual analog scale (VAS) ≥3 in neck and shoulder [17, 58, 65].

Concerning exclusion criteria, those are ineligible if pregnant during the study process, having surgery on the upper extremities during the past year, unable to perform exercise due to any medical conditions, and being in weight out of the normal range (18 ≥ BMI ≥ 25).

Drop out criteria are considered if the subjects attend no post-tests, lose three sequential intervention sessions, and any factors that may affect the study results.

However, the subjects are allowed to discontinue the study at any stage [66]. At the first encounter at baseline, the researchers are asked for permission to contact them in the case of study discontinuation. Accordingly, performing an accurate intention-to-treat analysis of the primary result is possible.

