### Outcome measures

Before randomization and at baseline, all assessments are performed and repeated after the intervention. NSP and sick leave due to pain are considered as the primary outcome variables, followed by the alignment, workability, and electromyography (EMG) activities of the selected muscles as the secondary variables. In the first part of the questionnaire, the subjects are asked to insert their demographic and social status including gender, age, weight, and height (body mass index = kg/m^2^), work hour/week, years of experience, education level, and marital status [71].

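### The stated harms question is asked at follow-up and covers training sessions only, so it gives no comparable control count and may miss events outside sessions and in people who leave

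*Protocol article*

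**What the plan says.** The harms question is the last sentence of the Intervention section of the Protocol article: "At the follow-up, subjects are asked whether they have experienced any injuries or other adverse events during the training sessions". It fixes a time (the follow-up) and a scope (events in training sessions).

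Follow-up is not defined separately. The only post-baseline assessment described is the one at the end of the 8 weeks. Under Outcome measures: "Before randomization and at baseline, all assessments are performed and repeated after the intervention".

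Three other passages bear on who can answer:

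- Study design describes the third arm as "a control group with no intervention performing routine activities".
- Subjects and eligibility criteria sets out who counts as lost: "Drop out criteria are considered if the subjects attend no post-tests, lose three sequential intervention sessions, and any factors that may affect the study results".
- The same section seeks "permission to contact them in the case of study discontinuation", and gives as its purpose an accurate intention-to-treat analysis of the primary result.

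The Intervention section also describes contact during the 8 weeks. Online sessions are supervised live three times a week. In the workplace group "supervision is conducted using diary and telephone interviews", and an expert attends once a week. On pain in a session: "If reporting pain during the exercise performance, the subjects can discontinue and rest until pain relief". The Randomization section puts the reporting of harms within the scope of the audit.

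**The concern.** This is a stated rule, not a detail left open, and its wording decides whose events can be counted. It has three weaknesses. A question about training sessions has no meaning for people who have none. An injury or flare of pain that appears in the hours or days after a session falls outside the wording. A question put at the end is not put to someone who does not come back, and a person hurt by the exercises has a reason not to come back. The answers also rest on recall over 8 weeks.

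All participants enter with neck and shoulder pain of at least 3 on the VAS, so some worsening is to be expected whatever the group. Without the same question in the controls, an event in an exercise group cannot be set against that background. Safety also bears on the trial's own question, because the two exercise groups differ mainly in how closely they are supervised.

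**Working it through.** The article reports no expected harm rate, so there is no figure to reproduce. The check sets the passages side by side and then sizes the possible effect under stated assumptions.

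**Who is covered by the question as worded**

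| Participant or event | Covered? | Reason |
|---|---|---|
| Exercise group, attends post-test, event in a session | Yes | Matches time and scope |
| Exercise group, attends post-test, event outside a session | No | Outside the stated scope |
| Exercise group, does not attend post-test | Not by this question | No other time is stated for it |
| Exercise group, missed three sessions in a row, still attends post-test | Possibly | Counted as a drop-out, but not said to be barred from the post-test |
| Control group, any event | No | No training sessions |

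**How many might not be asked.** The Sample size section raises 11 per group to 15. No loss rate is stated, so the implied margin is

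(15 − 11) / 15 = 4/15 = 26.7% per group.

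**Effect on the rate in an exercise group.** Let pc be the harm rate in 11 completers and pd the rate in 4 people lost; both are assumed. The true rate is (11·pc + 4·pd)/15, and the rate seen among those asked is pc.

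| pc | pd | True rate | Seen among 11 asked | Same events over 15 randomised |
|---|---|---|---|---|
| 10% | 10% | (1.1 + 0.4)/15 = 10.0% | 10% | 1.1/15 = 7.3% |
| 10% | 30% | (1.1 + 1.2)/15 = 15.3% | 10% | 7.3% |
| 10% | 50% | (1.1 + 2.0)/15 = 20.7% | 10% | 7.3% |

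The first row shows no bias among those asked. The rate is too low only if people who leave have more harms than those who stay, or if people who were not asked are counted as event-free.

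**Effect on the contrast with control.** The true excess is pE − pC, where pE and pC are the exercise and control rates. With the question as worded the control count is zero by construction, so the contrast becomes pE − 0 and is too large by pC. Background events that happen to surface in a session are therefore all charged to the exercise. This works against the loss of harmed participants, and the article gives no figures from which to say which effect is larger.

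**The case against.** A reader might infer that drop-outs and controls cannot report any harm at all, and that the trial's harm rate is therefore biased low. The documents do not support either statement.

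- The article does not say that this is the only channel. It is a condensed account, its procedure table is not shown, and the audit covers the reporting of harms. Other collection may exist.
- There is regular contact during the intervention through live sessions, the diary, telephone interviews, a weekly visit and pain reporting in sessions. People who leave can be contacted if they have agreed to it.
- Someone who is a drop-out only for missing three sessions in a row may still attend the post-test.
- The most relevant harm, worse neck-shoulder pain, is a primary outcome together with sick leave due to pain. Both are measured before and after, with no exclusion of controls.
- A low bias is an assumption about who leaves, and the control zero pushes the contrast up, not down.

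All of this stands, and it limits the point. It does not remove it. None of the contacts is stated to record harms, and the permission to contact is tied to the primary result. An audit checks what has been reported; it does not collect answers from people who were not asked. The pain score and days of absence do not record an injury or another adverse event as such. The existing contacts show mainly that the repair is cheap.

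**Conclusion.** The point holds in a limited form. The one harms question that the article states cannot give a comparable control count, leaves out events outside sessions, and may miss people who do not attend the post-test. The first two follow from the wording alone. The third depends on whether anyone is reached after leaving, which the article does not state for harms.

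The size is not known. Up to 26.7% of a group not asked is a margin implied by the sample size, not a planned loss rate. The gap between 10% seen and 15.3% to 20.7% true rests on assumed rates. Under-counting in the exercise groups requires that harmed people leave more often, or that people not asked are treated as event-free. The structural zero in controls would overstate the excess against control. The primary and secondary efficacy analyses are not affected. The change should be made because it is inexpensive and gives safety counts that can be compared between groups.

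**What to change.** Reword the last sentence of the Intervention section so that:

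1. The same open question is put to all three groups. It covers any injury, new or worse pain, or other adverse event since randomisation, and is not limited to training sessions.
2. It is asked at the post-test and, using the contact permission already sought, at discontinuation. The purpose of that permission in Subjects and eligibility criteria should be widened to include harms.
3. Counts are reported by group with both the number asked and the number randomised, so that people who were not asked are not read as event-free.
4. Events noted in the existing session, diary and telephone contacts are logged for safety but kept out of the between-group comparison.

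The cost is one item on the post-test form, a short contact with each person who leaves, and a line in records that are already kept. The small downside is that the exercise groups are contacted more often than controls, so the running log would find more events in them. Item 4 deals with this by resting the comparison on the common question alone.

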
**Fig. 2 Fig2:**
[figure not shown]
Workplace corrective exercises. **1** Sitting position: arms in a W shape, horizontal abduction with external rotation. **2A**, **2B** Sitting position: chin tuck. **3** Sitting position: scapula retraction and depression with arms in a T shape. **4A**, **4B** Sitting position: scapula retraction overhead and arms overhead. **5A**, **5B** Sitting position: forward flexion starting with the arms parallel with the body. **6A**, **6B** Sitting position: elevation 90° flexed elbows in the scapular plane with 30° external rotation by an elastic band. **7A**, **7B** Sitting position: dynamic hug exercise by the elastic material as resistance performing bilateral, maximum scapular protraction. **8** Sitting position: horizontal arm 90 abduction with external rotation. **9A**, **9B** Sitting position: extension starting with the arm at 90° of forward flexion. **10A**, **10B** Sitting position: thoracic extension exercises

**Fig. 3 Fig3:**
[figure not shown]
Online-supervised corrective exercises. **1** Supine position: arms in a W shape and horizontal abduction with external rotation. **2A**, **2B** Sitting position: chin tuck. **3** Prone position: scapula retraction and depression with arms in a T shape. **4A**, **4B** Standing position: scapula retraction overhead and arms overhead. **5A**, **5B** Side-lying position: forward flexion starting with the arms parallel with the body. **6A**, **6B** Prone position: extension starting with the arm at 90° of forward flexion. **7** Prone position: horizontal arm 90 abduction with external rotation. **8A**, **8B** Sitting position: thoracic extension exercise. **9A**, **9B** Standing position: Elevation 90° flexed elbows in the scapular plane with 30° external rotation by the elastic band. **10A**, **10B** Standing position: dynamic hug exercise by the elastic material as resistance performing bilateral, maximum scapular protraction

The detailed exercise program is available for administration by two interventions groups in Figs. 2 and 3.

### Outcome measures

Before randomization and at baseline, all assessments are performed and repeated after the intervention. NSP and sick leave due to pain are considered as the primary outcome variables, followed by the alignment, workability, and electromyography (EMG) activities of the selected muscles as the secondary variables. In the first part of the questionnaire, the subjects are asked to insert their demographic and social status including gender, age, weight, and height (body mass index = kg/m^2^), work hour/week, years of experience, education level, and marital status [71].

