**Methods and design:**

To this end, 45 subjects within the age range of 30–45 years are randomly assigned to three groups in the present parallel-group, randomized control trial using a pretest-posttest design. These groups include the subjects who receive online-supervised exercise and workplace exercise containing three sessions of intervention for 8 weeks and the control group receives no intervention while performing routine activities. The primary outcome variables are neck-shoulder pain (NSP) and consequent sick leave due to NSP, followed by alignment, workability, and the surface electromyography of upper, middle, and lower trapezius (UT, MT, and LT), sternocleidomastoid (SCM), and serratus anterior (SA) as the secondary variables.

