### Objectives

Given the explanations mentioned earlier, the present study seeks to evaluate the effect of workplace-based versus online-supervised home-based corrective exercises containing NSP and sick leave due to NSP as the primary objectives.

The secondary objectives include workability, alignment (i.e., neck, shoulder, and thoracic spine angles), and assessing the surface EMG of designated muscles including UT, MT, LT, SCM, and SA among office workers with UCS.

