#### NSP intensity

To determine NSP intensity, the subjects are asked through a questionnaire to mark a vertical line on the VAS line at the point which represents their pain intensity in each area (i.e., head, neck, shoulder, and upper back) on a scale ranging from 0 to 10 representing no pain and severe, respectively [71, 72].

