#### Workability and sick leave due to pain

Workability is self-assessed using the related questionnaires by a single validated item from the workability index [73, 74]. The subjects respond to one question as to how they rate their current workability according to their capabilities to meet the mental and physical demands of their job, which can still perform in two years. The response scores range from 0 to 10, indicating inability to work and workability with a cut-off point score of ≤7 implying poor workability, respectively [75]. In addition, sick leave due to pain is evaluated using a single item from the validated Outcome Evaluation Questionnaire to obtain data on the number of absence days from work due to pain in muscles or joints within the past month, and response categories ranged from 0 to 31 days [76]. Based on a recent meta-analysis, self-reported sick leave demonstrates good reliability and validity against the records [77].

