### Statistical method and analysis

Data are analyzed using IBM SPSS statistics software, version 24 for Windows, and descriptive statistics are applied to describe the variables considering sig. ≤0.05. Further, data normality is reported based on the Shapiro-Wilk test.

A 3 (group) × 2 (time) mixed-model repeated-measures ANOVA is used to compare all values from the pre-test to each point of the time within each group. Furthermore, the mixed-model repeated-measures ANOVA is applied to analyze within-group changes. Additionally, Bonferroni’s post hoc test for indicating the significance is utilized for any significant difference, and one-way ANCOVA is employed to compare the groups in the post-test with each pre-test value as a covariate. In addition, the effect size is calculated for the magnitude of the difference using the partial *η*2 method as small (0.01 ≤ *η*2 < 0.06), medium (0.06 ≤ *η*2 < 0.14), or large (*η*2 ≥ 0.14). It should be noted that interim analyses were not planned in the present study.

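### Two unranked primary outcomes share one 0.05 level and NSP has no single score, so the family-wise error is up to about 10% if either outcome can support a claim

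*Protocol article*

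**What the plan says.** Three places in the protocol article name the same two primary outcomes without ordering them. The abstract has "The primary outcome variables are neck-shoulder pain (NSP) and consequent sick leave due to NSP", the Objectives have "containing NSP and sick leave due to NSP as the primary objectives", and Outcome measures has "NSP and sick leave due to pain are considered as the primary outcome variables".

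The NSP intensity section asks subjects to mark "their pain intensity in each area (i.e., head, neck, shoulder, and upper back) on a scale ranging from 0 to 10". It gives no rule for combining the four marks or choosing among them. Eligibility (Subjects and eligibility criteria) uses a VAS of at least 3 in the neck and shoulder only. Sick leave is one item, "the number of absence days from work due to pain in muscles or joints within the past month".

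Statistical method and analysis sets the level in one sentence: "descriptive statistics are applied to describe the variables considering sig. ≤0.05". It then applies a 3 × 2 mixed ANOVA to all values and an ANCOVA of the post-test with the pre-test as covariate. Bonferroni appears once, as the post hoc test that follows a significant difference. The Sample size section uses an undivided alpha of 0.05 and an effect size of 0.66 taken from a study of neck pain.

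**The concern.** A post hoc Bonferroni test acts within an outcome, among the comparisons that follow a significant overall result. It leaves untouched the error that arises from having two primary outcomes. The text contains no order of testing, no division of alpha, and no requirement that both outcomes succeed. Applied as written, it gives the trial two chances at 0.05 to report a positive primary result.

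The undefined NSP score adds to this. With four marks per subject and no primary score fixed in advance, the reported NSP result could be chosen after the data are seen. The Discussion expects employers and clinicians to use the findings, so the strength of the primary claim matters, particularly with 45 subjects.

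**Working it through.** **Inputs from the protocol article.** Two primary outcomes; significance level 0.05; three groups of 15 (N = 45); sample-size inputs of alpha 0.05, power 80% and effect size 0.66, giving 11 per group.

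**Assumptions not in the article.** The correlations between outcomes, taken over a range below, and the premise that either primary outcome alone can support a claim.

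**1. The plan's own figure.** Take 0.66 as Cohen's f in a two-group F test at alpha 0.05. Noncentral-F power is 0.837 at 11 per group and 0.797 at 10, so the stated 11 is reproduced with alpha undivided. This reading is not the only one: f = 0.33 (half of 0.66) in a two-group pre-post interaction with correlation 0.5 also gives 11. Other readings do not reproduce it. Three groups with f = 0.66 need 9 per group, and Cohen's d = 0.66 needs 37 per group two-sided by the normal approximation.

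**2. Two primary tests at 0.05 each.**
- Independent: 1 − 0.95² = 0.0975.
- Upper bound under any correlation: 0.05 + 0.05 = 0.10.
- Positively correlated: simulated three-group F tests, 15 per group, 20,000 replicates per setting.

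| Assumed correlation | Chance of at least one false positive |
|---|---|
| 0 | 0.099 (exact 0.0975) |
| 0.3 | 0.094 |
| 0.5 | 0.092 |
| 0.7 | 0.084 |
| 0.9 | 0.070 |

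**3. Neck VAS, shoulder VAS and sick leave tested separately.**
- Independent: 1 − 0.95³ = 0.143.
- Simulated, with sick leave correlated 0.3 with each pain score: 0.137, 0.127 and 0.119 for neck–shoulder correlations of 0.5, 0.7 and 0.8.

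**4. With control across the two outcomes.**
- Under a fixed order, NSP keeps the full 0.05 used in the sample-size calculation, and the family-wise error is at most 0.05.
- Under Holm, the smaller p-value is compared with 0.025. If 0.66 is Cohen's f, power for one outcome at 0.025 with 15 per group, before dropout, is 0.887 (two-group F) or 0.952 (three-group F). If 0.66 is Cohen's d, power with 15 per group is 0.33 at 0.025, but it is already only 0.44 at 0.05.

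These figures count one test per outcome. The article applies both the mixed ANOVA and the ANCOVA and names neither as primary. That adds a further, highly correlated chance of error that is not counted here.

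**The case against.** The strongest reply is that this is a journal article and a separate SAP may exist. Testing order and score derivation are often left to a SAP, and the article states no success rule. If both primary outcomes had to be significant, there would be no inflation. The last point stands as a condition on the result. The rest does not dispose of the matter, because the article is not silent: it fixes two primary outcomes, one 0.05 level, and a post hoc role for Bonferroni. Followed as written, those rules leave the error across the primary outcomes uncontrolled.

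It is also fair to say that pain and sick leave due to pain are probably positively correlated, so that doubling is a ceiling for two tests. That is correct, and the range in the working reflects it.

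Two stronger readings are tempting and are not supported.
- A reader might count all four VAS areas plus sick leave as five primary tests, which gives 1 − 0.95⁵ = 0.226 if independent and about 0.13 to 0.22 under the assumed correlations. The article says that four areas are recorded. It does not say that four are tested as primary. The outcome's name and the eligibility criterion point to neck and shoulder, and the sample size rests on neck pain.
- A reader might multiply five muscles, onset and amplitude, and three movement phases into a long list of secondary tests. The EMG section does not say that results are analysed by phase. These outcomes are labelled secondary, so they do not bear on the error of the primary claim. Reporting unadjusted secondary outcomes is common and is not an error in itself.

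**Conclusion.** The point holds at moderate size. If either primary outcome can support a claim, the family-wise error is up to about 10% instead of 5%: 9.75% under independence and about 7 to 9% for correlations of 0.9 to 0.3. The correlations are assumptions, but the 10% bound does not depend on them. The missing single NSP score could raise the figure to about 12 to 14% if neck and shoulder were tested separately beside sick leave. It would go higher only if all four areas were treated as primary tests, which the article does not state. This should be corrected because the stated rule itself produces the inflation and the correction costs very little.

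**What to change.** Add one paragraph to the protocol and the registry entry, by the amendment route described under Randomization and before any post-test data are examined:

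- Define NSP as one score per subject from the neck and shoulder VAS, for example their mean, since these are the sites used for eligibility. Make head and upper back secondary.
- Test NSP at 0.05, and test sick leave at 0.05 only if NSP is significant. Alternatively, use Holm over the two.
- State which model, the mixed ANOVA or the ANCOVA, supplies the single p-value for each primary outcome, so that the order applies to one test each.
- Report alignment, workability and EMG as estimates with confidence intervals, without confirmatory claims.

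The fixed order needs no additional subjects because NSP stays at the alpha used for the sample size. Its cost is that sick leave cannot be claimed alone if NSP fails. Holm would allow such a claim if the sick-leave p-value were at most 0.025, at the price of a stricter first step.
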